### Statistical analyses and power calculations

Based on a standard deviation (SD) for baseline weight of 15 kg, and a correlation between repeat measures of r = 0.90 (obtained from our previous studies involving similar populations), our study has 90 % power using a two-sided 5 % level of significance to detect a clinically important difference in change in body weight of 4 kg between any pair of groups with 42 participants per group. While this may be viewed as a large difference, anything smaller does not really represent a difference of any importance between strategies. Thus we will recruit 250 participants in total across the five groups which allows for 15 % drop-out/unusable data. Fifty per group at baseline also provides 80 % power to detect differences of 5 cm in waist circumference (baseline SD 12, r = 0.80).

The primary analysis will follow modified intention-to-treat principles (using all available data) and will compare the outcomes resulting from the five different support strategies (*RCT analysis*). Linear mixed models will be used to model outcomes at 6, 12 and 24 months after adjusting for baseline values. Standard mixed model diagnostics will be performed. Although this analysis does not take diet and exercise choice into account because meta-analyses show there is little difference in outcomes from different treatments, further analysis adjusting for diet and exercise will be considered.

However, because participants do have choice over which diet and exercise plan they would like to follow, we are able to investigate the data in a number of ways. The baseline data will allow a *cross-sectional analysis* to assess the popularity of approaches among participants and then to examine what it is about people that lead them to choose to follow these different diet and exercise approaches (subject to sufficient numbers choosing each approach). Once the RCT analysis has been completed, we will be able to undertake a *cohort analysis* to determine whether adherence differs for each of the different diet and exercise approaches, subject to sufficient numbers making that particular choice, and how this differing adherence affects our study outcomes of interest.

All analyses will be performed using Stata 13.1 or a later version with all statistical tests performed at the two-sided 0.05 level.

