### Aims and objectives

The goal of our study is to determine whether allowing participants to choose from a selection of appropriate diet and exercise plans, within the context of a randomised controlled trial evaluating four different support strategies, enhances adherence and promotes greater weight loss and positive health outcomes. Giving people the choice of which diet and exercise regime is best incorporated into their particular lifestyle is expected to improve adherence, reflects real-world conditions, and is consistent with the lack of evidence for meaningful differences between diet modalities. Acknowledging this concept in conjunction with testing different support strategies offers a unique opportunity to determine how best to support individuals to make dietary and exercise changes under real-world conditions.

The primary aim of our study is to determine the effectiveness of different support strategies (control condition, brief support, daily self-weighing, app use, hunger training) on weight loss at 12 and 24 months. Secondary aims are to determine:(i)the effect of different support strategies on body composition, dietary intake, exercise, inflammatory markers, blood lipids and lipoproteins, adiponectin, ghrelin, and psychosocial indices at 12 and 24 months(ii)the degree of adherence to each of the support strategies over the 24 months(iii)the degree of adherence to each of the diet (Mediterranean, intermittent fasting, modified Paleo) and exercise (current recommendations, HIIT) plans that are selected over the 24 months and the outcomes within these self-selected groups.

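### The stated 90 % power for a 4 kg weight difference holds for a baseline-adjusted mean of two follow-up weights, which the protocol does not name; at 12 or 24 months alone it is about 78 to 80 %, and the waist power is understated

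*Protocol article*

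**What the plan says.** The section on statistical analyses and power calculations of the protocol article starts from these inputs: "Based on a standard deviation (SD) for baseline weight of 15 kg" and "a correlation between repeat measures of r = 0.90". It then claims that "our study has 90 % power using a two-sided 5 % level of significance to detect a clinically important difference", namely a "difference in change in body weight of 4 kg between any pair of groups with 42 participants per group". It treats 4 kg as the smallest difference between strategies that matters. Allowing for 15 % loss, it arrives at 50 per group and 250 in total. A second claim follows: "Fifty per group at baseline also provides 80 % power to detect differences of 5 cm in waist circumference", with SD 12 and r = 0.80.

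Under Aims and objectives, the primary aim concerns the effect of the support strategies "on weight loss at 12 and 24 months". Under Study design, month 12 closes the intervention, and month 24 is a later follow-up to see whether changes last. The planned analysis is a linear mixed model for the 6-, 12- and 24-month outcomes, adjusted for baseline. The article does not say how many follow-up weights entered the power calculation, nor that they were averaged.

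**The concern.** A power figure belongs to one contrast. As worded, this one belongs to a difference in weight change between two groups, and a reader will attach it to the two visits in the primary aim. A calculation for one visit with the stated SD and correlation needs 57 to 60 per group for 90 % power, not 42.

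What is at stake is how a null result is read. Because 4 kg is presented as the smallest difference of interest, a reader of a non-significant pairwise result at 12 or 24 months would assume a 10 % chance of having missed it. On the article's own inputs that chance is 20 to 22 %.

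**Working it through.** **Inputs** (all from the power section): weight SD 15 kg, r = 0.90, difference 4 kg, two-sided 5 %, 42 per group, 15 % loss; waist SD 12 cm, r = 0.80, difference 5 cm, 50 per group. I assume the same SD at every visit and the same correlation between every pair of visits.

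**Formulas.** With one baseline and the mean of p follow-ups, the effective SD is

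- change score: SD × √[(1 + (p − 1)r)/p + 1 − 2r]
- baseline-adjusted: SD × √[(1 + (p − 1)r)/p − r²]

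The number per group is n = 2 × (1.960 + z)² × (effective SD / difference)², with z = 1.2816 for 90 % and 0.8416 for 80 %. Power is Φ(difference / (effective SD × √(2/n)) − 1.960).

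**Reproducing the plan's figure.** With p = 2 and baseline adjustment, the effective SD is 15 × √(0.95 − 0.81) = 5.61 kg and n = 41.4, so 42 per group. Power at 42 is 90.4 % (89.8 to 90.2 % with the noncentral t). Then 42/0.85 = 49.4, so 50 per group and 250 in total. The stated numbers are recovered.

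**Weight, all variants**

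| Contrast | Effective SD (kg) | n per group for 90 % | Power at 42 | Detectable with 90 % power at 42 (kg) |
|---|---|---|---|---|
| One visit, change | 15 × √0.20 = 6.71 | 59.1 → 60 | 78.0 % | 4.75 |
| One visit, baseline-adjusted | 15 × √0.19 = 6.54 | 56.1 → 57 | 80.1 % | 4.62 |
| Mean of two, change | 5.81 | 44.3 → 45 | 88.4 % | 4.11 |
| Mean of two, baseline-adjusted | 5.61 | 41.4 → 42 | 90.4 % | 3.97 |
| Mean of three, change | 5.48 | 39.4 → 40 | 91.7 % | 3.87 |
| Mean of three, baseline-adjusted | 5.27 | 36.5 → 37 | 93.6 % | 3.73 |

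With the noncentral t, the single-visit powers are 77.1 to 77.6 % (change) and 79.1 to 79.7 % (baseline-adjusted). With no loss at all (50 per group) they are about 85 % and 86 %. A one-sided 5 % test at 42 gives 86.2 % and 87.7 %, so sidedness does not explain the gap.

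Forty-two is also the single-visit, baseline-adjusted answer for 80 % power: 2 × (1.960 + 0.8416)² × (6.54/4)² = 41.9. So 42 fits two contrasts at two different powers, and the article does not say which was meant.

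**Waist**

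| Contrast | Effective SD (cm) | Power at 42 | Power at 50 |
|---|---|---|---|
| One visit, change | 12 × √0.40 = 7.59 | 85.5 % | 90.9 % |
| One visit, baseline-adjusted | 12 × √0.36 = 7.20 | 88.9 % | 93.5 % |
| Mean of two, baseline-adjusted | 6.12 | 96.3 % | 98.3 % |

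The other variants (mean of two with change scores, mean of three either way) lie between 93.7 % and 98.0 % at 42 and are higher at 50. None returns 80 %. At a single visit, 80 % power needs only 37 (change) or 33 (baseline-adjusted) per group.

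**The case against.** The strongest defence is that the weight figure is right. A standard baseline-adjusted repeated-measures formula with two follow-ups returns exactly 42 at 90 %, the primary aim names exactly two time points, and the planned model is a baseline-adjusted mixed model. A condensed article may leave the number of follow-ups to a fuller document, and the waist figure is conservative and so harmless.

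Much of this stands. A reader might infer that 90 % cannot follow from the stated SD and correlation, or that the design as a whole delivers only 78 to 80 %. The documents support neither: one coherent method reproduces the figure, and the lower range applies to a contrast at one visit. A reader might also suspect that the 90 % and the 80 % were swapped between weight and waist. That is conjecture, since the recomputed waist power depends on the contrast and on whether 42 or 50 are counted, and the article gives no sign of a swap.

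The defence does not clear the text, for four reasons.

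- The article ties its power to a difference in weight change and mentions no average.
- Months 12 and 24 answer different questions, effect at the end of the intervention and persistence afterwards. Their mean answers neither, and an effect that fades would be diluted in it.
- The model covers three follow-ups, and averaging all of them gives 37 or 40 per group, not 42. With complete data, a mixed model adds essentially nothing to a contrast at a single visit.
- The method that recovers the weight figure gives 96 to 98 % for waist, so the second claim does not confirm it as the method used.

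The point therefore does not rest on a missing detail. A printed figure, read with the stated aim, describes a different contrast.

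**Conclusion.** The concern holds in a limited form. The 90 % is reproducible, but for the baseline-adjusted mean of two follow-up weights. For a pairwise comparison at 12 or at 24 months, 42 per group gives about 78 % (change) to 80 % (baseline-adjusted), some 10 to 12 percentage points below the stated figure. The waist power is understated by at least 5 points with 42 per group, and by about 11 to 13 points at a single visit with the stated 50.

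These results rest on the article's SDs and correlations, taken as equal at all visits and between all pairs of visits. That the two-follow-up average was the intended method is an inference from the numerical match and the two time points in the aim; the article does not state it. The matter deserves correction because readers will lean on the figure when interpreting null comparisons, but it is not a critical defect and does not call the sample size into question.

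**What to change.** Keep 250 participants and change the power paragraph in one of two ways.

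1. If the average was intended, name the mean of the 12- and 24-month weights, adjusted for baseline, as the contrast with 90 % power at 42 per group, and add that power for 4 kg at a single visit is about 80 %.
2. If the visits are to be judged separately, state about 80 % power for a 4 kg baseline-adjusted difference at a given visit with 42 per group, or equivalently 90 % power for about 4.6 kg.

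In either case, restate the waist power on the same basis. For a single visit that is about 86 to 89 % for 5 cm with 42 per group, or 91 to 93 % with 50.

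The cost is a few sentences and, for a single visit, a less favourable headline figure for weight. No extra participants, visits or analyses are needed.

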**Methods/design:**

SWIFT (Support strategies for Whole-food diets, Intermittent Fasting, and Training) is a two-year randomised controlled trial in 250 overweight (body mass index of 27 or greater) adults that will examine different ways of supporting people to make appropriate changes to diet and exercise habits for long-term weight control. Participants will be randomised to one of five intervention groups: control, brief support (monthly weigh-ins and meeting), app (use of MyFitnessPal with limited support), daily self-weighing (with brief monthly feedback), or hunger training (four-week programme which trains individuals to only eat when physically hungry) for 24 months. Outcome assessments include weight, waist circumference, body composition (dual-energy x-ray absorptiometry), inflammatory markers, blood lipids, adiponectin and ghrelin, blood pressure, diet (3-day diet records), physical activity (accelerometry) and aerobic fitness, and eating behaviour. SWIFT is powered to detect clinically important differences of 4 kg in body weight and 5 cm in waist circumference. Our pragmatic trial also allows participants to choose one of several dietary (Mediterranean, modified Paleo, intermittent fasting) and exercise (current recommendations, high-intensity interval training) approaches before being randomised to a support strategy.

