### Screening appointment

Potentially eligible participants will attend a screening session following a 12-hour overnight fast. Duplicate measurements of height, weight, and systolic/diastolic blood pressure will be undertaken using standard techniques and venepuncture blood samples will be collected by a registered nurse. Participants will complete a comprehensive baseline questionnaire, and be instructed on how to complete a 3-day weighed diet record over the next week. Participants will also wear an Actigraph accelerometer for 7 days and nights to assess physical activity and sleep during the same time period. Further exclusion criteria will be applied at this point: measured BMI less than 27, fasting blood glucose greater than 7 mmol/L (if randomised to hunger training, fasting blood sugars consistently above 7 mmol/L would result in difficulties for the participant to adhere to hunger training guidelines), systolic BP greater than 160 mmHg or diastolic BP greater than 100 mmHg (because they require medical management for their hypertension). All participants will also undergo a dual-energy x-ray absorptiometry (DXA) scan at baseline (see outcome measures).

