
### Outcome assessments

Outcome assessments will occur at 0 (baseline), 6 (mid-point of intervention), 12 (end of intervention) and 24 (end of follow-up) months as shown in Table 1. Adherence measures are more frequent as outlined elsewhere.

**Table 1 Tab1:** Timing of outcome assessments in the SWIFT study^*^

Outcome	Month			
	0^†^	6	12	24
Height	x			
Weight^§^	x	x	x	x
Bioimpedance	x	x	x	x
DXA scan	x		x	
Blood pressure	x	x	x	x
Blood samples	x		x	x
3-day diet record	x	x	x	x
Accelerometry	x	x	x	x
Aerobic fitness	x	x	x	x
Questionnaires	x	x	x	x
Demographics	x			
Personality	x			
Resilience	x			
Dieting and weight history	x			
Intuitive eating	x	x	x	x
Dutch eating behaviour questionnaire	x	x	x	x
Depression, anxiety, stress	x		x	x
Disordered eating	x		x	x
Self-monitoring	x	x	x	x
Self-efficacy	x	x	x	x
Satisfaction with diet and exercise		x	x	x

^*^Two visits are required at each time point in order to complete all measurements

^†^0 refers to baseline

^§^More frequent weights will be available for those in the regular brief support and daily self-weighing groups but these are for adherence measures rather than outcomes

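### The stated 80 % power for waist circumference does not follow from its own inputs (they give about 90–93 % at 50 per group), and Table 1 has no waist row

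*Protocol article*

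**What the plan says.** All references are to the protocol article.

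- **Abstract, Methods/design:** "SWIFT is powered to detect clinically important differences of 4 kg in body weight and 5 cm in waist circumference".
- **Statistical analyses and power calculations, waist:** "Fifty per group at baseline also provides 80 % power to detect differences of 5 cm in waist circumference", with the inputs "baseline SD 12, r = 0.80".
- **Same section, weight:** baseline SD 15 kg, r = 0.90 and 90 % power for a "difference in change in body weight of 4 kg between any pair of groups with 42 participants per group". Total recruitment is 250 over five groups, which allows for 15 % loss.
- **Same section, analysis:** linear mixed models for 6, 12 and 24 months, adjusted for baseline, with "all statistical tests performed at the two-sided 0.05 level".
- **Outcome assessments:** visits at 0, 6, 12 "and 24 (end of follow-up) months as shown in Table 1". The table has separate rows for height, weight, bioimpedance, DXA and blood pressure, and goes down to individual questionnaires. It has no row for waist.
- **Anthropometry and body composition:** gives the technique for waist but no months. The same paragraph does give timing for bioimpedance (every time point) and DXA (0 and 12 months).

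**The concern.** Everything needed to check the waist power is printed: group size, difference, SD, correlation and significance level. If the result does not follow, either one of those inputs is misprinted or the calculation used a method that the article does not describe. A reader cannot tell which. The weight calculation stands in the same paragraph and also names no method, so it is the natural place to look for the missing convention.

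The schedule matters because waist is one of only two outcomes for which the article claims power. The waist calculation relies on a correlation with baseline, and the analysis adjusts for baseline. The schedule should therefore show plainly when waist is taken, including at month 0.

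**Working it through.** **Inputs (Statistical analyses and power calculations).** Waist: SD 12 cm, r = 0.80, difference 5 cm, 50 per group. Weight: SD 15 kg, r = 0.90, difference 4 kg, 42 per group. Both use two-sided 5 %. The evaluable number after 15 % loss is 50 × 0.85 = 42.5, taken as 42.

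**Effective SD, one follow-up.**
- Change score: SD × √(2(1 − r)). Waist: 12 × √0.40 = 7.59. Weight: 15 × √0.20 = 6.71.
- Baseline-adjusted: SD × √(1 − r²). Waist: 12 × √0.36 = 7.20. Weight: 15 × √0.19 = 6.54.

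**Attempt to reproduce the stated 80 % for waist.** The standard error of the group difference is s × √(2/n), and √(2/50) = 0.20.
- Change score, n = 50: 5 / (7.59 × 0.20) = 3.29. Then 3.29 − 1.96 = 1.33, so power is 91 % (normal) or 90 % (t).
- Baseline-adjusted, n = 50: 5 / (7.20 × 0.20) = 3.47. Then 3.47 − 1.96 = 1.51, so power is 93 % by either.
- At n = 42, √(2/42) = 0.218. The t-based powers are 85 % (change score) and 88 % (baseline-adjusted).

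So 80 % is not reproduced. By the normal formula, 80 % needs only 37 (change score) or 33 (baseline-adjusted) per group. Equivalently, 50 per group has 80 % power for about 4.25 cm or 4.03 cm.

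**Does one method give both stated figures?** Averaging p follow-ups, each correlated at r with baseline and with each other (an assumption), replaces the variance factor:
- Change score: (1 + (p − 1)r)/p + 1 − 2r.
- Baseline-adjusted: (1 + (p − 1)r)/p − r².

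For p = 2, baseline-adjusted, the SDs are 12 × √(0.90 − 0.64) = 6.12 for waist and 15 × √(0.95 − 0.81) = 5.61 for weight. The t-based powers are:

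| Method | Weight, n = 42 (stated 90 %) | Waist, n = 50 (stated 80 %) | Waist, n = 42 |
|---|---|---|---|
| Change score, one follow-up | 77 % | 90 % | 85 % |
| Baseline-adjusted, one follow-up | 79 % | 93 % | 88 % |
| Change score, two averaged | 88 % | 96 % | 93 % |
| Baseline-adjusted, two averaged | 90 % | 98 % | 96 % |
| Change score, three averaged | 91 % | 98 % | 95 % |
| Baseline-adjusted, three averaged | 93 % | 99 % | 98 % |

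The weight figure reproduces with baseline adjustment over two averaged follow-ups. By that method waist is at 96–98 %. No row gives 80 % for waist.

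**Other variants.** A one-sided test moves waist power further above 80 %. A Bonferroni level for four comparisons (0.05/4 = 0.0125) with change scores at n = 50 gives 78.7 %. That is the nearest match, but the article states the 0.05 level. The stricter level would also lower the weight power below the single-visit values in the table, away from 90 %.

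**The case against.** The best defence is that the error is harmless. The stated power is too low, not too high. The 250 participants come from the weight calculation, and waist is an added remark about an outcome that is not primary. One could also read 80 % as a floor. The first two arguments stand: no sample size or analysis changes. The floor reading is weaker, since the neighbouring weight sentence ties an exact power to an exact n, and the waist sentence is worded the same way.

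A second fair objection is that the right replacement figure is not settled. The analysis covers three follow-ups, so a single-visit 85–88 % is not self-evidently the figure to print. This also stands. It is why the restated power has to name its method.

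Two stronger readings are tempting.

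- **That the trial is underpowered for waist.** The stated inputs show the opposite at the 5 % level that the article sets.
- **That no baseline waist is planned, so power collapses and the adjusted analysis cannot be run.** A reader might infer this from Table 1, or from the Screening appointment section and the aims, neither of which names waist. The article does not support it. Outcome assessments are set for 0, 6, 12 and 24 months. The anthropometry paragraph groups waist with weight and restricts only DXA to certain months. The power section uses a baseline waist SD and adjusts for baseline. The screening section also leaves out bioimpedance and aerobic fitness, which Table 1 schedules at month 0, and the aims do not name blood pressure, which Table 1 schedules at every visit. Silence in those places shows little.

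**Conclusion.** The waist power is misstated in the conservative direction. On the printed inputs it is about 90–93 % rather than 80 % at 50 per group, and about 85–88 % at 42, for a pairwise comparison at one follow-up and two-sided 5 %. Averaging follow-ups raises it further, assuming that repeat measures share the stated correlation. The sample size is unaffected.

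The more informative part is the inconsistency within the paragraph: of the methods tried, none returns both 90 % for weight at 42 per group and 80 % for waist at 50. Either the two sentences rest on different unstated methods or an input is misprinted. The article does not let a reader decide which.

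The absence of waist from Table 1 is a schedule omission to be reconciled with the abstract, the anthropometry paragraph and the power section. It is not evidence that waist goes unmeasured.

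**What to change.** 1. Restate the waist power from its stated inputs, naming the method (change score or baseline-adjusted), the number of follow-ups and the evaluable n. For example: 85–88 % at 42 per group for a single follow-up.
2. Use the same method for weight and waist, and say so. The choice has a consequence. With two averaged follow-ups and baseline adjustment, the weight figure stands at 90 % and waist becomes about 96 % at 42 per group. With a single visit, waist is 85–88 %, but weight at 42 per group is 77–79 % and that sentence would need restating too.
3. If the SD, the correlation or the significance level in the waist sentence is a misprint, correct that input instead and keep the power that follows from it.
4. Add a waist row to Table 1 at the assessment months, including baseline.

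The cost is a reworded sentence or two and one table row. Recruitment does not change because of the waist figure, and the waist technique is already described.

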### Randomisation

Once participants have chosen their diet and exercise approach, randomisation will occur using sequentially numbered opaque sealed envelopes prepared by the statistician. The participants will be stratified by sex and random length blocks will be used to allocate the treatment. Participants will then be booked into their first intervention session.

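### Randomisation is stratified by sex, but the stated primary model does not name sex as a covariate: a small, conservative loss of precision that one phrase would remove

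*Protocol article*

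**What the plan says.** The Randomisation section gives one stratification factor: "The participants will be stratified by sex and random length blocks will be used to allocate the treatment".

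The section on statistical analyses and power calculations then sets out the primary analysis, which compares the five support strategies using all available data: "Linear mixed models will be used to model outcomes at 6, 12 and 24 months after adjusting for baseline values". The same paragraph goes on to the participants' own choice of diet and exercise plan. It says that the primary analysis does not take this choice into account, gives a reason, and adds that "further analysis adjusting for diet and exercise will be considered". Sex is mentioned neither as a covariate nor as something left out.

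**The concern.** Blocking within sex makes the arms nearly equal in their mix of men and women, so a sex difference in outcome contributes almost nothing to the true variability of an arm contrast. A model without sex cannot credit the design for this. It places any sex difference that baseline does not explain in the residual, and the reported standard error then exceeds the real sampling variability. Confidence intervals come out wider than the design warrants, tests reject slightly too rarely, and power is lower than it could be.

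The paragraph discusses adjustment explicitly, bringing one variable in and setting two aside, yet passes over the one factor built into the allocation. An analyst who followed the sentence as written would not use the stratification. What is at stake is precision in the weight contrasts and, in principle, in the other outcomes analysed with the same model.

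**Working it through.** **Inputs from the article** (statistical analyses and power calculations): "Based on a standard deviation (SD) for baseline weight of 15 kg"; "a correlation between repeat measures of r = 0.90"; "our study has 90 % power using a two-sided 5 % level of significance"; a "difference in change in body weight of 4 kg between any pair of groups with 42 participants per group"; and a total of 250 allowing for 15 % drop-out or unusable data.

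**Inputs not in the article, therefore assumed:** the share R² of the post-baseline residual variance that sex explains; or, equivalently, the sex difference D in follow-up weight after baseline adjustment (0 to 4 kg) and the share of women p (0.5 to 0.65).

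**Step 1: reproduce the plan's own figure.** For a baseline-adjusted comparison of the mean of m follow-ups, with equal correlations r, the residual SD is 15 × √[(1 + (m − 1)r)/m − r²].

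- m = 2: 15 × √(0.95 − 0.81) = 15 × √0.14 = 5.612 kg. Then n = 2 × (1.960 + 1.282)² × 31.5/16 = 41.4, rounded up to 42 per group; power at 42 is 0.904.
- m = 1: 15 × √(1 − 0.81) = 6.538 kg. Power at 42 is 0.801.
- Drop-out: 42/0.85 = 49.4, rounded up to 50 per group, and 5 × 50 = 250.

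The stated 42 and 250 are thus reproduced with two follow-ups averaged and without any use of sex. The sample size does not depend on sex adjustment.

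**Step 2: cost of leaving sex out, by share of variance.** With sex balanced across arms, adjustment multiplies the residual variance by (1 − R²). The inflation from omission is 1/√(1 − R²) − 1.

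| Assumed R² | Standard error too wide by |
|---|---|
| 0 | 0 % |
| 0.02 | 1/√0.98 − 1 = 1.0 % |
| 0.05 | 1/√0.95 − 1 = 2.6 % |
| 0.10 | 1/√0.90 − 1 = 5.4 % |

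**Step 3: the same for weight, in kilograms.** R² = D² × p(1 − p)/SD². For example, D = 4, p = 0.5 and m = 2 give 16 × 0.25/31.5 = 0.127, so the standard error is 7.0 % too wide. With m = 2 and 42 per group, over p = 0.5 to 0.65:

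| D (kg) | Standard error too wide by | Power with sex added (0.904 without) |
|---|---|---|
| 0 | 0 % | 0.904 |
| 1 | 0.4 % | 0.906 |
| 2 | about 1.5 % | 0.912 to 0.913 |
| 3 | 3.4 to 3.8 % | 0.922 to 0.924 |
| 4 | 6.3 to 7.0 % | 0.935 to 0.938 |

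With one follow-up the inflation runs from 0 to 5.0 %, and power moves from 0.801 to at most 0.838.

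**Step 4: simulation.** Five arms of 50, exactly balanced on sex (60 % women), one follow-up, no drop-out, residual SD 6.54 kg; 8,000 runs under no effect and 4,000 under a 4 kg effect.

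| D (kg) | Without sex: mean SE / empirical SD | Type I error without / with sex | Power for 4 kg without / with sex |
|---|---|---|---|
| 0 | 1.309 / 1.299 | 0.047 / 0.047 | 0.863 / 0.863 |
| 1 | 1.313 / 1.301 | 0.046 / 0.046 | 0.871 / 0.872 |
| 2 | 1.322 / 1.307 | 0.047 / 0.049 | 0.862 / 0.865 |
| 4 | 1.361 / 1.305 | 0.041 / 0.047 | 0.836 / 0.855 |

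The direction is as expected: without sex, the standard error overstates the true variability and the test becomes conservative. The effect is visible only at the top of the assumed range.

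**The case against.** The strongest objection is that this is a condensed article. It does not say that baseline is the sole covariate, and the full covariate list may stand in an analysis plan that is not shown. A reader might infer from the sentence that sex is deliberately excluded; the text does not support that, since only diet and exercise choice are said to be left out. This objection limits the finding but does not remove it. The article does describe the adjustment of the primary model, and as described the model does not reflect the randomisation. If another document already names sex, the remedy is a clarifying phrase.

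The second objection is that the loss is conditional and probably small. Baseline weight, with an assumed correlation of 0.90 to follow-up, may already carry much of the sex difference. A residual difference of 4 kg would equal the whole effect the trial is designed to detect. This stands: up to 2 kg the inflation is under 2 %. For the same reason it cannot be said outright that the standard errors are too wide. For waist, body composition, blood and fitness outcomes the article gives nothing from which a residual sex effect could be derived, and these too are adjusted for their baseline values.

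A reader might also link this to power and infer that the trial really has about 80 % for weight. The article does not settle that. The stated inputs give 90 % when two follow-ups are averaged and about 78 to 80 % for a single time point (0.780 for change scores, 0.801 with baseline adjustment), and the text does not say which applies. That is a separate question, and adding sex would not resolve it.

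**Conclusion.** The point holds in a limited form. Allocation is stratified by sex, and the primary model as described does not name it. To the extent that sex predicts the outcome beyond baseline, standard errors are somewhat too wide: about 1.0 %, 2.6 % or 5.4 % if sex explains 2 %, 5 % or 10 % of the remaining variance, and not at all if it explains none. For weight, an assumed residual sex difference of 0 to 4 kg corresponds to 0 to 7 %. These ranges rest on assumed sex effects and on near-exact balance within sex. Simulated type I error stays below 5 %, and the planned sample size is reproduced without sex adjustment, so neither validity nor the size of the trial is in question. Severity is minor: a free improvement.

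**What to change.** In the section on statistical analyses, state: *The linear mixed models for all randomised comparisons will be adjusted for the baseline value of the outcome and for sex (the stratification factor).*

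The cost is one phrase and, if the sex effect is held constant over visits, one extra parameter with about 212 to 250 participants (250 × 0.85 = 212.5). Sex is recorded for everyone at baseline, so no data collection changes. Fixing this in writing before analysis also removes a later choice between sex-adjusted and unadjusted results. If drop-out should differ by sex, having sex in the model makes the missing-at-random assumption behind an all-available-data analysis easier to defend.
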